### Randomization and Allocation

#### Stratified Randomized Groups

In this study, 48 APOE4 carrier AD patients (APOE4-AD) and 32 non-APOE4 carrier AD patients (Non-APOE4-AD) will be recruited. Then, they will be assigned to the HF-rTMS group and the LF-rTMS group based on the stratified randomization method: 40 for the HF-rTMS group and 40 for the LF-rTMS group, while in subgroups, 24 patients will be assigned to in the APOE4-HF group, 24 patients will be assigned to the APOE4-LF group, 16 patients will be assigned to non-APOE4-HF group, and 16 will be assigned to the non-APOE4-LF group. The specific process is as follows: Our team members consist of quality control personnel, TMS therapy physicians, neuropsychological assessors and laboratory staff. Specifically, quality control personnel are responsible for quality control of study data and grouping randomization; TMS therapy physicians perform TMS treatment based on information from quality control personnel; neuropsychological assessors conduct neuropsychological assessments before, during and after treatment and follow-up; laboratory staff are in charge of blood sample processing and testing. In addition, the grouping randomization information will not be released by quality control personnel until the primary endpoint of the study has been met for all program participants at follow-up (Table 1).

The postadmission randomization process are performed by the quality control staff. Specifically, the admission sequence of APOE4 carriers and non-carriers was 1–48 and 1–32, respectively, and the admission numbers of carriers and non-carriers were randomized using Excel sheet randomization to assign them within the HF-rTMS and LF-rTMS groups, respectively. When the follow-up of all subjects reached the clinical trial endpoint, the project quality control staff and the project leader verified the grouping information for unblinding and summarized the project data for statistical analysis.

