### Study Process

After AD patients are included in the study, their neuropsychological scales, including cognition, anxiety, depression, activities of daily living and other scales will be assessed. Then, they will be assigned to HF-rTMS or LF-rTMS group and accept due treatment for 2 weeks. During the treatment, the neuropsychological scales will be assessed every week. In addition, blood test results and 32-channel EEG data will be collected before and after treatment, while a 6-month follow-up will be carried out after treatment (Figure 1).

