### Sample Size Calculation

The sample size of this project was calculated by Pass software on the basis of previous literature. In this study, the MMSE scores of the HF-rTMS group and the LF-rTMS group were 10.4 ± 1.7 and 10.2 ± 1.8, respectively, before treatment. After 2 weeks of rTMS treatment, their MMSE scores reached 11.2 ± 1.9 and 8.8 ± 2.3, respectively (Ahmed et al., 2012), when the target effect size had 80% power (β = 0.10) and a type I error was 5% (α = 0.05). In addition, the group sample size of 13 and 12 achieved 81% power for detecting a difference of 2.4 between the null hypothesis and that the mean of both groups is 11.2 and the alternative hypothesis that the mean of Group 2 is 8.8 with known group standard deviations of 1.9 and 2.3 and a significance level (alpha) of 0.050 using a two-sided two-sample *t*-test, while the sample size of each subgroup is at least 13. Considering the loss of follow-up, falling off and sample data being eliminated due to data quality, the sample size should be increased by 20%. Thus, the final sample size of each subgroup are at least 16. Furthermore, the ratio of APOE4 carriers to non-APOE4 carriers are set to 3:2 according to the comparison of population samples and our previous study. Other than that, in this study, 80 participants, with 48 APOE4 carriers and 32 non-APOE4 carriers will be recruited.

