### Results in Progress

Our study is still in progress. Our current data are the preliminary data of the RCT study, and the grouping has not been unblinded. We analyzed the demographic informatics of APOE4 carriers and non-carriers and the changes in cognitive function scores before and after 2 weeks of rTMS treatment. More detailed information was displayed in Supplementary Table 1.

To date, 18 patients with clinically diagnosed Alzheimer’s disease have been included and have received rTMS treatment for 2 weeks. Among them, ten were APOE4 carriers; eight were non-carriers, and there were no significant differences in age, education or gender (Table 2). They were randomly assigned to the high-frequency treatment group or the low-frequency treatment group. Because the study was not blinded, we could not know which subgroup they were assigned to. We could only analyze the overall treatment effect. According to our preliminary results, there was no significant difference in MMSE score, MoCA score except ADAScog (Supplementary Table 1) score between the two groups before and after treatment. When comparing the improvement rate of the two groups, there was a significant difference in the improvement of MoCA score between the two groups. For non- carriers, the MoCA score but not the MMSE or ADAScog score improved by 2.65 ± 3.15, while for carriers, it improved by 0.1 ± 1.7 (*t* = 2.164, *p* = 0.046, Figures 2A–C).

**TABLE 2 T2:** Characteristics of the study cohort.

	APOE4 carriers (*n* = 10)	Non-APOE4 carriers (*n* = 8)	*p*-value
Sex F/M	6/4	5/3	0.914
Age, years	70.37.45	73.756.27	0.312
Education level, years	7.72.98	6.135.37	0.44
MMSE score before rTMS	12.66.77	15.888.54	0.377
MoCA score before rTMS	7.94.28	9.255.50	0.566
ADAScog score before rTMS	39.1316.49	34.8719.03	0.618
MMSE score after rTMS	13.56.22	16.638.73	0.388
MoCA score after rTMS	84.47	11.887.72	0.202
ADAScog score after rTMS	37.1616.39	31.5721.21	0.536

*n, number; F, female; M, male; MMSE, Mini Mental State Examination; rTMS, repetitive transcranial magnetic stimulation; MoCA, Montreal Cognitive Assessment Scale; ADAScog, Assessment Scale-cognitive subscale.*

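### With baseline MMSE this variable and allocation balanced on genotype alone, an HF-LF comparison of MMSE with no baseline term loses most of its precision; adjust for baseline MMSE.

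*Protocol article*

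**What the plan says.** - **Allocation (Stratified Randomized Groups).** Patients are stratified by APOE4 status, and within each genotype "the admission numbers of carriers and non-carriers were randomized using Excel sheet randomization to assign them within the HF-rTMS and LF-rTMS groups". The cell sizes are fixed: "24 patients will be assigned to in the APOE4-HF group, 24 patients will be assigned to the APOE4-LF group", while "16 patients will be assigned to non-APOE4-HF group, and 16 will be assigned to the non-APOE4-LF group". No other balancing factor is named.
- **Order of events (Study Process).** The neuropsychological scales are taken on inclusion. "Then, they will be assigned to HF-rTMS or LF-rTMS group". Baseline MMSE is therefore known before allocation.
- **Planned effect (Sample Size Calculation).** The design "achieved 81% power for detecting a difference of 2.4 between the null hypothesis" and the alternative (means 11.2 and 8.8 after treatment), "with known group standard deviations of 1.9 and 2.3 and a significance level (alpha) of 0.050". The planning study's baseline SDs were 1.7 and 1.8.
- **Analysis (Statistical Analysis Methods).** Groups are compared by independent-sample t-test, or by rank-sum test if non-normal, and repeated data by repeated-measures ANOVA. No baseline covariate is mentioned.
- **Order of testing (Statistical Hypothesis).** The hypothesis is superiority of HF over LF on MMSE, at end of treatment and the 3-month follow-up. In the subgroup analysis, HF and LF are compared first in non-carriers, then in carriers if P is below 0.05.
- **Interim data (Table 2, row "MMSE score before rTMS").** Carriers 12.6 with spread 6.77 (n = 10); non-carriers 15.88 with spread 8.54 (n = 8).

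**The concern.** The trial was sized from a study in which patients barely differed in baseline severity. This trial admits anyone with an MMSE up to 26 (lower cut-offs at lower education, no floor), and its own interim data show a baseline spread about four to five times larger. With 16 or 24 patients per arm within a genotype, random allocation on genotype alone will often leave HF and LF apart at entry by more than the effect sought.

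What is at stake is precision and readability. A baseline gap carries over into later MMSE. If the comparison uses the later score alone, the gap goes into the estimated effect. The first within-genotype test falls on the non-carriers, who have the smallest cells and the larger SD, and it decides whether the carriers are tested at all. A gap in one genotype but not the other would also be hard to tell from the genotype-specific response that the trial is looking for.

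**Working it through.** **1. The plan's own figure.** With known SDs, SE = √(1.9²/13 + 2.3²/12) = 0.848, and power = Φ(2.4/0.848 − 1.96) = 80.8%. The stated 81% reproduces as a comparison of post-treatment means with no baseline term.

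**2. Are the Table 2 spreads SDs?** The methods section speaks of mean ± standard error, so this needs a check. A t-test on 12.6 (6.77, n = 10) against 15.88 (8.54, n = 8), with the spreads taken as SDs, gives p = 0.376; Table 2 prints 0.377. They are SDs.

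**3. Chance baseline gap.** Within a genotype, the HF-LF difference in mean baseline MMSE has SE = SD × √(2/n) and P(|gap| > 2.4) = 2 × [1 − Φ(2.4/SE)].

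| | SD | n per arm | SE | P(gap > 2.4) |
|---|---|---|---|---|
| Carriers | 6.77 | 24 | 1.95 | 21.9% |
| Non-carriers | 8.54 | 16 | 3.02 | 42.7% |

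- At least one genotype: 1 − 0.781 × 0.573 = 55.2%.
- Same calculation with the planning baseline SDs (1.7 and 1.8): about 0.02%.
- Pooled comparison, genotypes weighted 48:32: SE = √(0.6² × 1.954² + 0.4² × 3.019²) = 1.68, so P = 15%.

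**4. Uncertainty in the SDs.** The 95% chi-square limits are 4.66 to 12.36 (carriers) and 5.65 to 17.38 (non-carriers). With both SDs at their lower limits, the probability for at least one genotype is 29%; with both at their upper limits, 85%. The upper end is loose: scores between 0 and 26 cannot have an SD much above 26/2 = 13.

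**5. How much carries over.** The MMSE pre-post correlation is not reported. The MoCA figures in Results in Progress imply one for that scale:
- non-carriers: (5.50² + 7.72² − 3.15²)/(2 × 5.50 × 7.72) = 0.94
- carriers: (4.28² + 4.47² − 1.7²)/(2 × 4.28 × 4.47) = 0.93

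If these held for MMSE, each baseline point would carry over as r × SD(post)/SD(pre): 0.93 × 6.22/6.77 = 0.85 in carriers and 0.94 × 8.73/8.54 = 0.96 in non-carriers.

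**6. What baseline adjustment gains.** With equal pre and post SDs, the variance is proportional to 1 for a post-score test, 2(1 − r) for a change score and 1 − r² for ANCOVA. The reduction from ANCOVA is therefore r² against the post-score test and (1 − r)/2 against the change score.

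| r (assumed) | Against post-score t-test | Against change score |
|---|---|---|
| 0.80 | 64% | 10% |
| 0.93 | 86% | 3.5% |
| 0.94 | 88% | 3% |

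**7. What balancing the allocation would add.** In a simulation at r = 0.90 with baseline MMSE as a covariate, the SD of the estimated HF-LF difference was 1.39 under the present scheme and 1.34 with MMSE-banded allocation of the remaining patients in non-carriers, and 0.79 under both in carriers. Across the settings considered, the further variance gain is about 0 to 8%.

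**The case against.** The strongest reply is that nothing here is invalid. Randomisation within genotype to fixed totals is sound, chance imbalance under it is not bias, and the same large SD that produces the gap also widens the standard error, so the test keeps its level. All of that stands.

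A reader might infer from the 55% that the randomisation is defective and must be replaced. The documents do not support that. The 55% counts a gap in either direction in either genotype and rests on SDs from 18 patients. For the overall HF-LF comparison, which is the stated hypothesis, it is 15%. Once baseline MMSE is a covariate, rebalancing adds little. Nor do the documents support poor overlap between arms: a 2.4-point gap is only 0.28 SD in non-carriers (2.4/8.54) and 0.35 SD in carriers (2.4/6.77). They also give no evidence that the frequency effect depends on severity.

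A second reply is that repeated-measures ANOVA is listed, and the interim results already compare improvement. A group-by-time contrast or a change score would remove most of a baseline gap. That also stands, and it is why the gain against a change-score analysis is only 3 to 10%. But the article does not say which method carries the MMSE comparison, and the sizing is a t-test on post-treatment means, which removes none of the gap.

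Third, the article is condensed, and a separate analysis plan may already specify adjustment. If it does, the point reduces to aligning the Sample Size Calculation and Statistical Methods sections with it.

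**Conclusion.** The point holds as one of precision and interpretability. With allocation balanced on genotype only and the baseline SDs in Table 2, a baseline HF-LF gap larger than the planned effect is common within genotypes: about 22% in carriers, 43% in non-carriers and 55% in at least one (29 to 85% over the SD limits). In the pooled comparison it is less common, at 15%. A t-test on post-treatment MMSE leaves this variation in the estimate.

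The size of the loss depends on two things that the article does not settle. One is the MMSE pre-post correlation: 0.80 to 0.94 is an assumption, its upper end borrowed from MoCA over two weeks, and the month-3 value may differ. The other is whether the t-test is applied to scores or to changes. Against post-scores, adjustment removes 64 to 88% of the residual variance; against changes, 3 to 10%.

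**What to change.** Amend Statistical Methods so that the HF-LF difference in MMSE at week 2 and at month 3, overall and within each genotype, comes from a baseline-adjusted analysis. This can be ANCOVA, or a repeated-measures model of the post-baseline visits, with baseline MMSE as covariate. In the overall comparison, add APOE4 stratum as a factor. Make this the analysis on which the sequence in Statistical Hypothesis is tested, and fix it before the grouping is unblinded.

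The cost is one model term. No extra patients, visits or measurements are needed, because baseline MMSE is already taken before assignment.

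Optionally, the patients not yet allocated (80 − 18 = 62 at the time of writing) could be balanced on baseline MMSE within genotype, by bands or by minimisation with a random element. This would add only about 0 to 8% in variance once the covariate is used. It also needs a documented mid-trial change of scheme, with any bands cut at medians from 8 and 10 patients, so the recommendation does not depend on it.

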### Repetitive Transcranial Magnetic Stimulation Therapy

HF-rTMS group: The rTMS therapy are performed by a transcranial magnetic stimulator (XY-K-JLC-D, Xiangyu Medical, China).

#### TMS Target: Left Dorsolateral Prefrontal Cortex (L-DLPFC)

The patients accepted 14 consecutive days of TMS therapy (twice a day), with each treatment lasting for 30 min (110% of motor threshold, 20 Hz, 1 s, 29 s interval, 1200 pulses per treatment, 33,600 total sessions).

LF-rTMS group: The rTMS therapy was performed by transcranial magnetic stimulator (XY-K-JLC-D, Xiangyu Medical, China).

#### TMS Target: Left Dorsolateral Prefrontal Cortex (L-DLPFC)

The patients accepted 14 consecutive days of TMS therapy (twice a day) with each treatment lasting for 30 min (110% of motor threshold, 1 Hz, he stimulation time 40 s, 20 s interval, 1200 pulses per treatment, 33,600 total sessions).

### Localization of Transcranial Magnetic Stimulation Target

First, the skull surface position of the left precentral gyrus are located. Specifically, the midpoint of bilateral cerebral hemispheres will be confirmed by that of the patient’s bilateral tragus above the skull. Then, the location of the superior sagittal sinus was identified by connecting the nasal root position, the midpoint of bilateral cerebral hemispheres and the external occipital protuberance. It should be mentioned that the midpoint of this line is that of the superior sagittal sinus, which corresponds to the location of the central sulcus. Then, the skull surface position of the hand representation area in the central anterior gyrus was measured by 5 cm left siding from this midpoint in a direction perpendicular to the sagittal line. Furthermore, the left dorsolateral prefrontal region, the target area for rTMS, was located at 20% of the sagittal sinus length from this point in parallel to the sagittal line in a forward translation.

### Study Process

After AD patients are included in the study, their neuropsychological scales, including cognition, anxiety, depression, activities of daily living and other scales will be assessed. Then, they will be assigned to HF-rTMS or LF-rTMS group and accept due treatment for 2 weeks. During the treatment, the neuropsychological scales will be assessed every week. In addition, blood test results and 32-channel EEG data will be collected before and after treatment, while a 6-month follow-up will be carried out after treatment (Figure 1).

### Neuropsychological Assessments

The Mini Mental State Examination (MMSE), Montreal Cognitive Assessment Scale (MoCA) and Alzheimer’s Disease Rating Scale cognitive subscales (ADAS-cog) will be used to assess cognitive function, while the Generalized and Center for Epidemiologic Studies Depression Scale (CES-D) will be adopted to assess the mood of all the participants. In addition, daily activity is measured using the Activity of Daily Living (ADL) scale. All scales are tested with common forms and unified guidelines. The evaluators all have received standardized training and they will communicate with the subjects in local language.

### EEG Acquisition and Calculation and Analysis of EEG Metrics

EEG data will be collected via a high-density 32-channel EGI system (g.tec) with a sampling rate of 500 Hz and a mastoidea reference. During the recording, patients are instructed to stay awake, relax, and close their eyes for 10 min. Then, a bandpass filter (from 0.5 to 200 Hz) and a notch filter at 50 Hz and 100 Hz were applied. In addition, EEG will be collected under the condition of eyes closed, followed by preprocessing via MATLAB software, such as baseline adjustment, filtering, depression filtering, and referring. Finally, the changes in EEG power and spectra in different frequency bands before and after treatment of different genotypes were analyzed and compared.

EEG metric data will be processed and analyzed by MATLAB 2017. Beyond that, power spectral density (PSD), median spectral frequency (MSF) and spectral entropy measure dynamics of brain signals at a single electrode site are based on spectral frequency content.

For the main analysis, 10 EEG metrics: PSD in delta (1–4 Hz), theta (4–8 Hz), alpha1 (8–10 Hz), alpha2 (10–13 Hz), beta 1(13–20 Hz), beta 1(20–30 Hz), gamma1 (30–48 Hz), and gamma1 (48–100Hz) will be calculated, and then averaged across all epochs (60 s recording).

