## Objectives

The primary objective of the study is to analyze the different efficacies of rTMS in AD patients with different APOE genotypes, so as to provide the basis for the precise treatment of AD.

The secondary objective is to analyze the changes in gamma oscillations and pathological indicators in different APOE genotypes, thus being conducive to the precise treatment of AD.

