### Outcomes

The primary end point is the quantitative index, namely MMSE, whereas the secondary outcome measures are MoCA, ADAS-cog, GAD-7, CES-D, and ADL.

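### The upper gamma band (48–100 Hz) contains the plan's own 50 Hz notch and ends on its 100 Hz notch; a free, minor correction of the band limits avoids both

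*Protocol article*

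**What the plan says.** All the signal-processing statements are in the protocol article, section EEG Acquisition and Calculation and Analysis of EEG Metrics.

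- Recording: the EEG is taken "with a sampling rate of 500 Hz and a mastoidea reference".
- Filtering: "a bandpass filter (from 0.5 to 200 Hz) and a notch filter at 50 Hz and 100 Hz were applied". The width, order and type of the notch are not given.
- Bands: the list ends with "gamma1 (30–48 Hz), and gamma1 (48–100Hz) will be calculated". Both bands carry the same label; they are called lower and upper gamma here. Nothing says that notched frequencies are left out of the upper band.
- Broadband measures: the section also names "power spectral density (PSD), median spectral frequency (MSF) and spectral entropy measure dynamics of brain signals", with no frequency range for the last two.
- Comparison: "the changes in EEG power and spectra in different frequency bands before and after treatment of different genotypes were analyzed and compared".

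On the role of gamma, the Objectives section states: "The secondary objective is to analyze the changes in gamma oscillations and pathological indicators in different APOE genotypes". The Outcomes section makes MMSE primary, and "the secondary outcome measures are MoCA, ADAS-cog, GAD-7, CES-D, and ADL"; no EEG measure is listed there.

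**The concern.** Two stated choices do not fit together. The filter removes signal at 50 Hz and 100 Hz, and the upper gamma band is then drawn so that 50 Hz lies 2 Hz above its lower limit and 100 Hz is its upper limit. The lower gamma band avoids the mains by stopping at 48 Hz; the upper band starts there and runs straight across it.

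There are two consequences. Band power is reduced by an amount set by an unstated notch width. And if the notch does not remove all the mains, what remains is counted as gamma power. The first effect is much the same at every visit. The second need not be, because mains pickup can change from one recording to the next. Upper gamma is one of only two gamma bands serving the secondary objective, which concerns change in gamma, so variation between visits is the part that matters.

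**Working it through.** The plan gives no figure to reproduce. The inputs from the document are the notch centres (50 and 100 Hz), the bands (30–48 and 48–100 Hz), the passband (0.5–200 Hz) and the sampling rate (500 Hz). Notch width and type, the slope of the background spectrum and the behaviour of the mains are assumptions.

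**1. Overlap.** 48 < 50 < 100, and 100 Hz equals the upper limit. The lower band ends at 48 Hz, below 50 Hz. The overlap is therefore confirmed for the upper band only.

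**2. Power removed by the notches.** Take a background spectrum f^(−s) and ideal notches of full width w. Only the lower half of the 100 Hz notch lies in the band:

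loss = [∫ f^(−s) df from 50−w/2 to 50+w/2 + ∫ f^(−s) df from 100−w/2 to 100] / ∫ f^(−s) df from 48 to 100

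- s = 0: 1.5w/52, which is 2.9%, 5.8% and 11.5% for w = 1, 2 and 4 Hz.
- s = 1: for w = 4, [ln(52/48) + ln(100/98)] / ln(100/48) = 0.1002/0.7340 = 13.7%. For w = 1 and 2 it is 3.4% and 6.8%.
- s = 2: for w = 4, [(1/48 − 1/52) + (1/98 − 1/100)] / (1/48 − 1/100) = 0.001807/0.010833 = 16.7%. For w = 1 and 2 it is 4.2% and 8.3%.

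The range is about 3–17%. Second-order IIR notches have wider skirts: 4–6%, 8–11% and 15–19% in one pass, and 6–9%, 12–16% and 21–27% zero-phase, for w = 1, 2 and 4 Hz.

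**3. Cross-check by simulation.** The setting was 600 s of 1/f signal (SD 10 units) at 500 Hz, with the stated band-pass and a 2 Hz zero-phase notch. Power in 48–100 Hz fell from 11.876 to 10.266, a loss of 1 − 10.266/11.876 = 13.6%, within the 12–16% above.

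**4. What the loss does to a comparison.** Let r be the share of power kept. The before-after ratio is (r × post)/(r × pre) = post/pre, so r cancels. An absolute change is multiplied by r in every patient. With one filter throughout, the level is lowered and the contrast is barely affected.

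**5. Mains left after the notch.** With the 2 Hz zero-phase notch, steady mains at 50 and 100 Hz (50 Hz amplitude 2, 5 or 10) left band power at 10.266. Mains at 50.1 Hz raised it to at most 10.270 (+0.04%). With amplitude 5 at 50 Hz, plus a 100 Hz component at 30% of it, and unsteady mains, the addition to 48–100 Hz power was:

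| Notch | Drift 0.1–0.2 Hz | Amplitude modulated by 50% |
|---|---|---|
| 2 Hz zero-phase | 0–0.2% | 3% |
| 1 Hz one-pass | 5–17% | 18% |
| 0.5 Hz one-pass | 17–48% | 23% |

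For a 52–98 Hz band the addition was 0% in every case.

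**6. Effect of a residue that varies between visits.** If it adds 5% before treatment and 17% after (the ends of one cell above), the apparent ratio is 1.17/1.05 = 1.11: an 11% rise with no neural change. The reverse order gives 1.05/1.17 = 0.90.

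**7. The 150 Hz harmonic.** It lies in the passband and has no notch. The Nyquist frequency is 500/2 = 250 Hz, so 150 Hz does not alias, and it is outside 48–100 Hz. Adding it left band power at 10.266. Over 0.5–200 Hz, however, amplitudes of 2–10 moved median spectral frequency from 9.5 to 10.25–46.25 Hz, and spectral entropy from 0.819 to as low as 0.673. Over 1–100 Hz both stayed where they were (8.5 Hz and 0.851).

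**The case against.** The best defence is that the notches are there to remove mains and, if reasonably wide and zero-phase, they do. What is left is a fixed filter loss, which cancels in the relative before-after comparison. Notch width, bin exclusion and metric ranges are details that a journal article may leave to a fuller document. EEG is not a listed outcome, and the 30–48 Hz band still serves the gamma objective.

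Most of this stands, and it limits the point to a minor one. It does not remove it: the band limits and notch frequencies are both stated, and as stated they collide.

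A reader might infer three stronger things that the document does not support.

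- **That upper gamma partly measures line noise.** This needs a residue after notching, and none is reported. One can posit a peak 1 Hz wide at 5–10 times background: it adds about 11–33% for slopes 1/f to 1/f², but only 4/52 = 7.7% to 9/52 = 17.3% for a flat spectrum. Either range presupposes a notch that largely fails.
- **That the un-notched 150 Hz harmonic contaminates gamma.** It cannot, as step 7 shows. It could reach only median spectral frequency and spectral entropy, and only if they are computed above 100 Hz, which the article does not say.
- **That the genotype or arm comparison is biased.** Mains pickup belongs to the recording session. Nothing in the article suggests that it differs by arm or genotype, so the expected effect is extra variance.

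**Conclusion.** The point holds as a minor inconsistency between the stated filter and the stated band. The overlap itself needs no assumption. Its size does: about 3–17% of 48–100 Hz power is lost for ideal notches 1–4 Hz wide and spectra from flat to 1/f², with little effect on relative change. Residual mains ranges from negligible (2 Hz zero-phase notch with small drift; 3% under strong amplitude modulation) to 5–48% (one-pass notches of 0.5–1 Hz), on mains behaviour that is assumed. If present, it would add noise to the upper-gamma change. The lower gamma band does not contain either notch frequency, and MMSE and the listed secondary outcomes are unaffected. The broadband measures raise only a conditional point about a range that the article does not give.

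**What to change.** Define upper gamma as 52–98 Hz, or keep 48–100 Hz and leave the notched bins out of the average. State the choice together with the notch width and type. The limits 52 and 98 Hz clear an ideal notch up to 4 Hz wide (50 + 2 and 100 − 2); the skirts of a wide IIR notch would still reach slightly inside, so the same filter should be used for every recording.

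If median spectral frequency and spectral entropy are computed on the 0.5–200 Hz signal, limit them to a range below 100 Hz that excludes 48–52 Hz.

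Fix this before unblinding, which the Results in Progress section reports as still to come, and reprocess the recordings already made in the same way. The cost is a change of limits in the MATLAB processing and, for 52–98 Hz, (100 − 48) − (98 − 52) = 6 of 52 Hz of bandwidth. No new data are needed and patients are not affected.
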